### Randomization: sequence generation and allocation concealment

Patients are randomly assigned (1:1:1) in permuted blocks according to computer-generated random numbers (R version 3.4.1), to undergo either standard usual care or booklet exercise or in-bed cycling. The randomization is performed at the day of inclusion (within 24 h of admission) after patients have provided informed consent to participate (additional file 2). No stratification factors are used in the randomization algorithm. The randomized sequence is generated centrally by a researcher not involved in the testing. The allocation is delivered to the researcher responsible for the exercise interventions in sealed envelopes at the time of inclusion. Patients are informed about their allocation after baseline assessment (at days 0 or 1) has been completed. The researcher performing the baseline assessment is responsible for informing the patients about their allocation. The study allocation is blinded for the nurses, physiotherapists, and clinicians treating the patients; however, the researcher responsible for the exercise intervention and outcome assessor is unblinded. Even though blinding could limit the occurrence of bias when collecting and assessing data, the researchers involved in this study has no influence on treatment plans or evaluation of readiness for discharge. The risk of bias due to lack of blinding is therefore evaluated to be relatively low.

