## Measurement of outcome variables

The time points at which the different outcomes are assessed are depicted in Fig. 4. After inclusion in the study baseline testing is performed (Fig. 4, days 0 or 1). Daily during hospitalization, vital signs are noted, and blood samples are collected (Fig. 4, day 0 until discharge). At discharge, tests performed at baseline are repeated (Fig. 4). Follow-up visits take place 1 and 3 months after discharge, while a phone interview will take place 6 months after discharge (Fig. 4, follow-up).

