### Muscle strength and functional ability

Muscle strength is measured using the handgrip test (SAEHAN DHD-1 Digital Hand Dynamometer, SAEHAN Corporation, South Korea) as an indicator of overall muscle strength, while the 30-s chair stand test (CST) is used to evaluate the functional ability by measuring lower body strength. Both tests are performed at days 0 or 1, day 5, on discharge, and follow-up visits at 1 and 3 months after discharge.

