### Strategies for preventing loss to follow-up

As the study has a relatively long follow-up period, different strategies have been incorporated into the study to minimize loss to follow-up. In order to increase patient’s commitment to the study, the research personal is trying to establish a bond with the patient by having the same personal performing tests, instructing exercise sessions, and scheduling follow-up visits. As the patient is being discharged contact information (phone number and email address) is collected. The follow-up visits should be as flexible and convenient for the patient as possible; therefore, the follow-up visits are offered either as hospital or home visits. To minimize absences from planned follow-up visits, patients are reminded about their upcoming visit in the study. After completion of the first follow-up visit, the next visit is scheduled in advanced to reduce the risk of not being able to get hold of the patient.

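### Grip strength, chair stand, Barthel and EQ-5D-5L are assessed unblinded by staff who are also meant to train the patients, and the protocol's low-bias argument does not cover these outcomes

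*Protocol article*

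**What the plan says.** On blinding, the section on randomization and allocation concealment says that treating nurses, physiotherapists and clinicians are blinded, but that "the researcher responsible for the exercise intervention and outcome assessor is unblinded". It accepts that blinding could reduce bias in data collection and assessment. It then rates the risk as fairly low, on the ground that "the researchers involved in this study has no influence on treatment plans or evaluation of readiness for discharge".

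On who does what, Strategies for preventing loss to follow-up describes building a bond with the patient by "having the same personal performing tests, instructing exercise sessions, and scheduling follow-up visits".

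On timing, the randomization section says: "The allocation is delivered to the researcher responsible for the exercise interventions in sealed envelopes at the time of inclusion". Measurement of outcome variables places baseline testing after inclusion, on day 0 or 1. The protection described is for the patient: "Patients are informed about their allocation after baseline assessment (at days 0 or 1) has been completed". The next sentence adds: "The researcher performing the baseline assessment is responsible for informing the patients about their allocation".

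On the tests themselves, Muscle strength and functional ability says of handgrip and the 30-s chair stand: "Both tests are performed at days 0 or 1, day 5, on discharge, and follow-up visits at 1 and 3 months after discharge". Study questionnaires has EQ-5D-5L and Barthel Index-100 completed jointly with the patient at day 1, then repeated at discharge, 1 and 3 months, and by phone at 6 months. The pre-planned analysis compares the arms on change from baseline for all four, using linear mixed models.

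**The concern.** Grip strength and the chair stand depend on how hard the patient tries, and so on how the tester encourages. Barthel and EQ-5D-5L are completed with staff help, so prompting and scoring can vary. A tester who knows the arm, and who may have spent the admission training that patient, can influence these results without meaning to. Usual-care patients have no study exercise sessions, so any trainer-tester relationship differs by arm by design.

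The outcomes are analysed as differences in change from baseline. A shift in one arm at discharge or follow-up therefore enters the estimated treatment effect directly. A shift at baseline would do so as well, if the tester knew the arm by then. These four measures are the trial's strength, functional-ability and quality-of-life evidence, and the protocol's only argument for a low risk of bias concerns something else.

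**Working it through.** **Step 1: the plan's own figure.** The sample size is not in dispute. With a difference of 2 days, SD 3.5 days, two-sided alpha 0.025 and power 0.8:

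n per arm = 2 × (2.2414 + 0.8416)² × 3.5² / 2² = 58.2, rounded up to 59 (power 0.806).

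Allowing for 15% drop-out: 59 / 0.85 = 69.4, rounded up to 70. Three arms give 210, as stated.

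**Step 2: discharge and follow-up.** Two statements suffice. The outcome assessor is unblinded (randomization section), and the same staff are meant to test and train (retention section). The reason for a low risk is that researchers do not affect treatment plans or discharge readiness. Set against the outcomes:

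- Length of stay: covered. Treating staff decide on discharge and are said to be blinded.
- DXA (total and leg lean mass, total and trunk fat mass), BIA fat-free mass, plasma markers and accelerometry: largely independent of the assessor, though not because of the reason given.
- Grip strength, 30-s chair stand, Barthel Index-100, EQ-5D-5L: not covered. Discharge decisions have no bearing on how these are tested or scored.

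That is four of the eleven continuous secondary outcomes listed for the mixed models.

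**Step 3: baseline.** The stated order is inclusion, with delivery of the envelope to the exercise researcher; then baseline testing on day 0 or 1; then the patient is told, by the baseline assessor. The assessor must therefore learn the arm at some point. Nothing shown says that this happens only after testing, and nothing says that it happens before.

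**Step 4: illustration of size.** The documents give neither an SD for these change scores nor a size of bias, so both are assumed. Work in SDs of the change score, with 59 per arm, no true effect and two-sided 5%. A simple two-group comparison stands in for the mixed model.

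SE = √(2/59) = 0.184

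False-positive rate = P(Z > 1.96 − b/SE) + P(Z < −1.96 − b/SE)

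Here b is the total bias in the difference in change: the upward shift at follow-up plus any downward shift at baseline in the exercise arm.

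| Assumed shift (SD) | Follow-up only | Same shift also at baseline |
|---|---|---|
| 0 | 5.0% | 5.0% |
| 0.1 | 8.4% | 19.2% |
| 0.2 | 19.2% | 58.4% |
| 0.3 | 37.1% | 90.3% |

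The last column applies only if the tester knew the arm at baseline, which is not shown.

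In chair-stand units, assume an SD of change of 3 repetitions and 70 × 0.85 = 59.5 per arm. Then SE = 3 × √(2/59.5) = 0.55. A follow-up bias of 0.5 repetition gives P(Z > 1.96 − 0.5/0.55) = 14.7% in the favoured direction; 1 repetition gives 44%.

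**The case against.** The trial is declared open-label, and the protocol discloses that the assessor is unblinded and concedes that this can cause bias. Length of stay is not affected through the assessor. Most continuous secondary outcomes are instrument or laboratory measures, and DXA and BIA results are exported directly to data sheets. All of this stands, and it limits the concern to four outcomes. It does not rescue the low-risk statement, which is worded generally and rests on a reason that does not reach those four.

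A reader might infer that staff know the arm when they run the baseline tests, so that change scores are biased at both ends. The documents do not support that. The envelopes are sealed, their opening time is not given, and telling patients after baseline fits equally well with opening the envelope after baseline. The full protocol, not shown here, may settle the point.

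A reader might also infer that each patient's trainer runs all of that patient's tests. The retention section states an intention to use the same personnel, not a rule for every patient, and the randomization section names the roles separately. The overlap is intended, but its extent is unknown.

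Two further objections hold. EQ-5D-5L is self-reported by a patient who knows the arm, so a change of tester cannot remove that source of bias. And the error rates show what an assumed bias would do, not that one of that size is present.

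**Conclusion.** The concern holds in a limited form. At discharge and follow-up, the bias route for grip strength, chair stand, Barthel and EQ-5D-5L follows from what the protocol states. Its ground for rating the risk as low applies to length of stay only. This is a conclusion that does not follow from the reason given, rather than a detail left to another document. At baseline, exposure is possible but not shown.

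The size cannot be estimated from the documents. Under the assumptions above, a follow-up shift of 0.1 to 0.3 SD would raise a nominal 5% false-positive rate to between 8.4% and 37.1%, so even modest differences in encouragement or scoring would matter. The primary outcome and the sample size of 210 are untouched. Because the affected outcomes are secondary and two of the three remedies cost nothing, the changes should be made, but the main comparison does not depend on them.

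**What to change.** 1. In the randomization section, require the envelope to stay sealed until the baseline tests are entered and saved in REDCap. No cost; it settles the baseline question for patients still to be recruited.
2. Limit the low-bias statement to length of stay and to other outcomes that do not depend on the assessor, giving the reason that applies to each. Report and interpret grip strength, chair stand, Barthel and EQ-5D-5L as assessed unblinded. No cost; this applies to the whole trial.
3. Where the existing team allows, have grip strength, chair stand and Barthel at discharge and follow-up run from a fixed script by a team member who did not train that patient. Keep scheduling contact with the same person, so that most of the retention aim survives. The cost is some rota work and slightly less continuity of contact, at a time when COVID-19 has already led to missed visits. The documents do not give the team size, so feasibility is for the investigators to judge.

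Item 3 has limits. A tester who did not train the patient may still learn the arm, and self-report bias in EQ-5D-5L remains. Recruitment has run since April 2019, so the change would reach only the remaining visits; record its start date so that the two testing conditions can be told apart.

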## Methods/design

### Study design and study setting

The study is a single-center, randomized, superiority, open-label, controlled trial with three parallel experimental arms, nested in a prospective cohort study. Over a 3-year period, all patients hospitalized with suspicion of lower respiratory tract infection at the Emergency Department at Nordsjællands Hospital, Hillerød, Denmark, will be screened for eligibility. Based on a sample size calculation, a total of 210 patients hospitalized with CAP are randomized in a ratio of 1:1:1 to standard usual care or standard usual care combined with daily supervised physical training consisting of either in-bed cycling or booklet exercises as depicted in Fig. 2. The enrolment period began on 1 April 2019 and is estimated to be completed by 1 March 2022. All baseline and discharge tests are carried out at the Department of Pulmonary and Infectious Diseases, Nordsjællands Hospital, Hillerød, Denmark. The follow-up tests are carried out at Department of Pulmonary and Infectious Diseases, Nordsjællands Hospital, Hillerød, Denmark or as home visits.

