## Outcomes and timing of assessments

The attending physician will evaluate whether the patient is ready for discharge. Readiness for discharge is based on the modified Halm’s criteria for clinical stability in CAP [26]. Once the criteria are met, the different measurements scheduled for discharge will be performed. The different outcome variables and timing of assessments are listed in Table 2.

**Table 2 Tab2:** Outcome

Outcome domain	Specific measurement	Specific metric				Methods of aggregation			Time point
		Value at a time point	Change from baseline	End value	Time to event	Mean	Percent/proportion	Absolute number	
Length of hospital stay	Discharge date–admission date			x		x			Discharge
Readmission	Readmission date–discharge date				x		x	x	3 months
Mortality	Mortality date–discharge date				x		x	x	6 months
Total lean mass	DXA scan		x			x			Discharge
Total fat mass	DXA scan		x			x			Discharge
Total fat-free mass	BIA scan		x			x			Discharge
Leg lean mass	DXA scan		x			x			Discharge
Trunk fat mass	DXA scan		x			x			Discharge
Health-related quality of life	EQ-5D-5L		x			x			Discharge
Activities of daily living	Barthel Index-100		x			x			Discharge
Muscle strength	Hand grip strength		x			x			Discharge
Muscle endurance	30-s chair stand test		x			x			Discharge
Systemic inflammation	Plasma samples		x			x			Discharge
Physical activity	AX3 accelerometers		x			x			After discharge
Glucose metabolism	Oral glucose tolerance test		x			x			3 months
Diabetes status	HbA1c	x					x	x	3 months
Prior physical activity level	IPAQ questionnaire	x					x	x	3 months
Frailty	Frail scale questionnaire	x					x	x	3 months

*BIA* bioelectrical impedance analysis, *DXA* dual-energy x-ray absorptiometry, *EQ-5D-5L* health-related quality of life, *HbA1c* hemoglobin 1Ac, *IPQA* International Physical Activity Questionnaire

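### Treating staff are said to be blinded in an open-label trial with visible daily exercise sessions, so the low bias rating for a physician-decided length of stay is unsupported

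*Protocol article*

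**What the plan says.** The section on study design and setting describes a "single-center, randomized, superiority, open-label, controlled trial". The section on randomization and allocation concealment describes who knows the allocation:

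- Treating staff: "The study allocation is blinded for the nurses, physiotherapists, and clinicians treating the patients".
- Study staff: "the researcher responsible for the exercise intervention and outcome assessor is unblinded".
- Patients: "Patients are informed about their allocation after baseline assessment (at days 0 or 1) has been completed".

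The same section gives one reason for not worrying about this, namely that the trial's researchers have no say in treatment plans or in judging readiness for discharge. It concludes: "The risk of bias due to lack of blinding is therefore evaluated to be relatively low".

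Under Outcomes and timing of assessments, "The attending physician will evaluate whether the patient is ready for discharge", and that judgement is to be based on the modified Halm's criteria for clinical stability. The primary outcome is the time from admission to discharge.

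**The concern.** Blinding of the clinicians matters here because one of them decides when the primary outcome occurs. If the discharging physician knows that a patient is training every day, that knowledge can affect how soon the patient is judged ready to leave at a given clinical state. A difference in length of stay could then mix faster recovery with a different threshold for discharge.

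The article presents treating-staff blinding as a fact, but its own account of the interventions makes this hard to believe. Its reason for a low risk of bias concerns the researchers, who do not decide discharge. If the wording is carried into the results paper, readers will be told of a safeguard on the primary outcome that the described design does not plausibly provide.

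**Working it through.** **Step 1. The statements side by side.**

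- Label: open-label (Study design and study setting).
- Patients: told their arm after baseline assessment, so they can mention it to staff (Randomization).
- In-bed cycling arm: a daily supervised session of 30 minutes, 25 of them on a bed bike (In-bed cycling).
- Booklet arm: a daily supervised session of 30 minutes with strengthening and walking exercises (Exercise booklet).
- Control arm: usual care, with no such sessions.
- Concealing sessions from ward staff, or checking whether staff stayed blind: nothing described. The sealed envelopes conceal the sequence up to inclusion, not the sessions that follow.

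The visibility of the sessions is the stronger ground. The open-label label alone does not exclude masking of some roles.

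**Step 2. Does the rating follow from its reason?** The reason covers the researchers. The endpoint is set by the attending physician. The rating for length of stay therefore depends on the physician being blind, which Step 1 leaves unsupported.

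**Step 3. What the stability criteria do.** Tying readiness to the modified Halm's criteria narrows discretion. However, the recorded outcome is the discharge date minus the admission date (Table 2), not the time at which the criteria are met, and the physician still makes the judgement.

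**Step 4. The plan's own figure.** Inputs from the sample size section: difference 2 days, SD 3.5 days, two-sided level 0.025, power 0.8, drop-out 15%.

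- n per arm = 2 × 3.5² × (2.241 + 0.842)² / 2² = 58.2, rounded up to 59.
- 59 / 0.85 = 69.4, rounded up to 70 per arm, or 210 in total.
- Power with 70 × 0.85 = 59.5 evaluable per arm: 0.81.

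The stated sample size is reproduced and is not in dispute.

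**Step 5. Hypothetical illustration.** Assume no true effect, the planning SD, 59.5 evaluable per arm and a normal approximation. Let discretion alone shorten stay by b days in one exercise arm.

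- SE of a contrast = 3.5 × √(2 / 59.5) = 0.642 day.
- Chance of a significant result favouring exercise = P(Z > 2.241 − b / 0.642).

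| Assumed shift b (days) | False positive favouring exercise, per contrast |
|---|---|
| 0 | 1.25% |
| 0.25 | 3.2% |
| 0.5 | 7.2% |
| 1.0 | 24.7% |

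The article gives no figure for b. Both its size and its direction are assumptions.

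**The case against.** The strongest reply is that discharge follows stated clinical-stability criteria, so there may be little room for discretion. In addition, sessions occur once a day and are run by an exercise physiologist or a physiotherapist student, and no text says that the discharging physician sees them. Nurses very probably would; for the physician it is less certain. The article is also candid that the exercise researcher and outcome assessor are unblinded.

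Much of this stands. The criteria are a real mitigation, and the article does not establish that physicians are unblinded. What does not survive is the unqualified statement that they are blinded, or a rating that depends on it without saying so.

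A reader might infer three stronger points that the document does not support:

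- **That length of stay is biased in favour of exercise.** Nothing shows this. A physician could also keep a patient in hospital longer so that training continues, which would shift the result the other way.
- **That discharge testing distorts the comparison.** The tests are done once the criteria are met, but the article does not say that discharge waits for them. They are scheduled in all arms, so they have no bearing on blinding.
- **That a shorter stay without earlier stability must be discretionary.** The trial hypothesises benefits for strength and functional ability, so exercise could shorten stay through mobility alone.

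The absence of a supportive analysis is not itself a fault, since a statistical analysis plan that is not shown may contain one.

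**Conclusion.** The blinding statement is wrong as written: it claims a property that the described design does not plausibly deliver. The relatively low rating is unsupported for the primary outcome, because its stated reason leaves out the person who decides discharge. This rests on the article's description of the interventions, patient knowledge of allocation and the discharge process, not on evidence that bias occurred.

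The size of any bias cannot be derived from the document. Over assumed shifts of 0.25 to 1.0 day towards earlier discharge, the false-positive rate favouring exercise would run from 3.2% to 24.7% per contrast, against a nominal 1.25%. This shows that a shift well below the planned 2-day effect could matter; it does not estimate what will happen. The covariate adjustment and the less conservative multiplicity method in the planned analysis would change these figures somewhat.

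**What to change.** 1. In the randomization section, state that patients are unblinded and that treating staff cannot be assumed blinded. Alternatively, state how staff blinding is kept and how it is checked. Reconcile the result with the open-label label, the two intervention descriptions and the account of who judges readiness for discharge.
2. Withdraw the relatively low rating as it applies to length of stay.
3. Pre-specify one supportive analysis: time from admission to first meeting the trial's own clinical-stability criteria, with the same covariates and the same two contrasts as the primary analysis. The article says "Daily during hospitalization, vital signs are noted", and patient files are already a data source, so the variable can be derived wherever the components are recorded. Report it beside length of stay to help interpretation, with no rule that labels a discordant result as discretionary.

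The cost is a wording change, one derived variable and one extra model. The variable is resolved only to the day. It also depends on all components of the criteria being recorded; the article does not list them, so this should be confirmed first. The primary outcome, the sample size and the conduct of discharge stay as they are.

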## Scientific ethics statement

The study is performed according to the Declaration of Helsinki II [37] and is carried out in accordance with the rules in the Danish Act on Processing of Personal Data. All participants receive written and oral information about the study prior to inclusion and their provision of oral and written consent. The participants can always discontinue participation in the study with no obligation to provide a reason.

